| **Population:** | ***AIM 1***   - ***Patient stakeholders*** *will include with and surviving central nervous system (CNS) cancers, 15-24 years old at the time of study. Detailed inclusion criteria below.* - ***Medical stakeholders*** *will include physicians, nurses and medical assistants in the Children’s Hospital Colorado (CHCO) Neuro-Oncology Program.* - ***Sample size***   *Patient stakeholders*   - - *Maximum number of patient participants that can be enrolled is 35*   - *Minimum number of patient participants to be enrolled is 9)*   *Medical stakeholders*   - - *Maximum number of healthcare provider participants that can be enrolled is 30*   - *Minimum number of healthcare provider participants to be enrolled is 9*   ***AIM 2-3***   - ***Patient stakeholders*** *will include patients with and surviving cancer seen in the CHCO neuro-oncology clinic, CHCO Oncology Clinic, CHCO HOPE Survivorship program, or Seattle Children’s Hospital (SCH) survivorship program, diagnosed prior to age 18 years and 15-24 years old at the time of study.* - ***Medical stakeholders*** *will include physicians, advanced practice provider, and nurses and medical assistants in the CHCO neuro-oncology and oncology clinics, CHCO HOPE Survivorship Program, of the SCH Survivorship Clinic* - ***Sample size***   *Patient stakeholders*   - - *Maximum number of patient participants that can be enrolled is 120*   - *Minimum number of patient participants to be enrolled is 86 (43 pre- and 43 post-implementation of screening approach)*   *Medical stakeholders*   - - *Maximum number of healthcare provider participants that can be enrolled is 50*   - *Minimum number of provider participants to be enrolled is 24 (surveys), 10 (semi-structured interviews), and 5 (brief interviews)* |
| **Study Design:** | *To adhere to NCCN AYA and Survivorship Guidelines, we will be developing and implementing a standardized screening approach for sexual function using the PROMIS SexFS Brief. This intervention will be implemented clinic-wide as standard of care for patients age 15-24 years with or surviving childhood cancer. While the intervention is the use of the screening tool/approach described below, patient responses to the screening measure will not be collected. Separate survey data for the aforementioned endpoints will only be collected for consenting/assenting participants.* |

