## **9.2 AIM 2 Statistical plan**

**Aim 2. Evaluate the preliminary effectiveness of the standardized screening approach for SD on occurrence of patient-provider SD communication.**

Analytic Plan: Descriptive statistics (means, medians, standard deviations, frequencies) will be computed for patient characteristics, overall and stratified by study period. Differences in patient predictors between study periods will be assessed using chi-squared and t-tests (or appropriate bivariable tests based on variable type and distribution).

The primary analysis will compare the effect of the intervention on the proportion of patients that self-report SD screening. We will use a multivariable logistic regression model for the binary outcome of self-reported SD screening, controlling for patient-level predictors identified a priori to be potential confounders (e.g., age, gender, presence of SD concerns, endocrinopathies, clinic site, on therapy or survivor). Although there is correlation due to the hierarchical structure of the data (patients within sites), due to the limited number of sites (<5), we will include a fixed effect for site rather than a random effect. The specific model will be of the form:

η_i_ = β_0_ + β_1_T_i_ + β_2_’Z_i_, (1)

where η_i_= log (ϕ_i_/ (1 - ϕ_i_)), is the log odds of success for patient i (i.e., patient i self-reported SD screening), T_i_ is an indicator of whether the measurement was taken in the pre-intervention (T_i_=0) or post-intervention (T_i_=1) period, Z_i_ is a vector of patient-level predictors including the site at which they were seen. To assess the intervention effect, we test the null hypothesis H_0_: β_1_=0 vs. H_1_: β_1_ ≠ 0. We will perform a subgroup analysis by key variables (site, therapy/survivor status) using an interaction between the subgroup variable and the intervention period. The secondary outcome of whether a patient reported that their SD need was met will be analyzed similarly, overall and in the subgroup of those that indicated that they had an SD need, which will be assessed using an interaction with the SD need indicator and the pre-/post- indicator.

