We will also use similar multivariable regression models adjusted for the same covariates to assess the effect of the intervention on secondary and exploratory outcomes. The secondary outcome of patient satisfaction measured on a 0-10 scale will be modelled as a continuous outcome using a multivariable linear regression model. The exploratory outcome of feasibility of collecting EHR data will be modelled as a binary outcome (yes/no documented/detected SD) using a logistic regression model. The exploratory outcome of number of referral patterns will be modelled as a count outcome using a multivariable Poisson regression model. To examine whether the intervention effect differs by key variables (site, therapy/survivor status) we will assess for an interaction effect between study period (pre/post) and the variable.

Goodness-of-fit tests and model-fitting diagnostics will be performed for proposed analyses to assess for influential points, outliers, and to evaluate alternative model specifications. All hypothesis tests will be two-sided with alpha=0.05, and p-values and confidence intervals will be reported. Statistical analyses will be conducted using R or SAS version 9.4 (SAS Institute Inc., Cary, N.C.).

Power: Sample size calculations are based on the number of participants needed pre- and post-implementation of the screening approach to detect a 25% difference in proportion of patients reporting SD conversations with their providers (5% pre-intervention vs. 30% post-intervention), aggregated across all sites. Assuming a multivariable logistic regression in which 20% of the variability in the independent variable is explained by the other predictors, to detect a clinically relevant difference of 25% (5% pre-intervention vs. 30% post-intervention) in SD conversations with a two-sided test, 80% power, and alpha =.05, 86 participants will be required (43 pre- and 43 post-implementation of screening approach).

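### At 43+43 with about 15 expected events, the primary logistic model can leave the period effect without a finite estimate (about 11% of trials), and the stated 80% power does not hold for a default Wald test

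*Protocol*

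**What the plan says.** Section 9.2 (Aim 2 Statistical plan) gives the primary model: "We will use a multivariable logistic regression model for the binary outcome of self-reported SD screening, controlling for patient-level predictors identified a priori". The covariates are given as examples: age, gender, presence of SD concerns, endocrinopathies, clinic site, and on therapy or survivor. Site enters as a fixed effect, and section 8.1 has four sites. The hypothesis is that the period coefficient, beta1, is zero. No test statistic is named. On error rates: "All hypothesis tests will be two-sided with alpha=0.05".

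The power paragraph assumes that "20% of the variability in the independent variable is explained by the other predictors" and concludes: "5% pre-intervention vs. 30% post-intervention) in SD conversations with a two-sided test, 80% power, and alpha =.05, 86 participants will be required". The synopsis uses the same figure as a floor ("Minimum number of patient participants to be enrolled is 86 (43 pre- and 43 post-implementation of screening approach") and sets a ceiling ("Maximum number of patient participants that can be enrolled is 120").

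Section 9.2 also plans interactions: "We will perform a subgroup analysis by key variables (site, therapy/survivor status) using an interaction between the subgroup variable and the intervention period". For sparse data it has only a general sentence on fit tests, diagnostics and looking at other model forms.

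**The concern.** Ordinary maximum likelihood breaks down when one period has no events. The period coefficient runs off to infinity, its standard error runs off faster, and the Wald p-value tends to 1. Yet zero conversations before implementation and many after is the strongest result the trial could produce for the intervention. The plan promises p-values and confidence intervals, and in that case a Wald interval would mean nothing.

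The choice of test also matters in every other trial. With this few events the Wald and likelihood-ratio tests of the same coefficient differ clearly in power and in type I error. A power statement that does not say which test it describes is therefore incomplete.

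**Working it through.** **Inputs from the protocol.** Rates 5% and 30%, 43 per period, two-sided alpha 0.05, 80% power, R-squared 0.20 (all section 9.2); four sites (section 8.1).

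**Not in the documents, so assumed.** Covariate prevalences, covariate effects and clinic shares. The simulations varied endocrinopathy over 10-40%, SD concerns over 25-50%, the log odds ratio for SD concerns over 0-3, and used equal or unequal sites, with 600-3,000 trials per setting.

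**1. The plan's own N.** Pooled two-proportion formula, with mean rate 0.175:

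n = [1.96 x sqrt(2 x 0.175 x 0.825) + 0.8416 x sqrt(0.05 x 0.95 + 0.30 x 0.70)]^2 / 0.25^2 = 35.06 per group, or 70.1 in total.

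Dividing by (1 - 0.20) gives 87.6, against 86 stated. The power of this formula at 43 x 0.8 = 34.4 effective patients per group is 79.2%. The figure reproduces closely.

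**2. Events and parameters.** 43 x 0.05 = 2.15 pre and 43 x 0.30 = 12.9 post, 15.05 in total. Slopes if all examples are used, with linear age and binary gender: 1 + 1 + 1 + 1 + 3 (site) + 1 (therapy) + 1 (period) = 9. That is 15.05/9 = 1.7 events per slope.

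**3. No finite period estimate.** P(no pre-phase event) = 0.95^43 = 11.0%. P(at most one) = 0.110 + 43 x 0.05 x 0.95^42 = 36%. The 11% arises with no covariates at all.

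**4. Wald power, closed form.** Log odds ratio = ln(0.30/0.70) - ln(0.05/0.95) = 2.097.
- No covariate correlation: SE = sqrt(1/(43 x 0.05 x 0.95) + 1/(43 x 0.30 x 0.70)) = 0.775. Power = Phi(2.097/0.775 - 1.96) = 77%. Exact enumeration of the unadjusted test gives 77.2%.
- R-squared 0.20: SE = 0.775/sqrt(0.8) = 0.866. Power = Phi(2.097/0.866 - 1.96) = 67.8%. For 80% power the same formula needs 57.6 per group, about 116 in total.

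**5. Simulation of the 9-slope model, 43+43, 5% vs 30%.**

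| Setting (realised R-squared) | Any infinite coefficient | Period infinite | Wald power | LR power |
|---|---|---|---|---|
| Moderate covariates (0.09) | 21.1% | 11.1% | 76.9% | 90.7% |
| Moderate (0.20) | 22.2% | 12.3% | 69.6% | 86.0% |
| Moderate (0.28) | 20.8% | 10.7% | 67.1% | 82.1% |
| SD-concern log OR 1.5 (0.22) | 19.2% | 10.3% | 74.5% | 88.1% |
| SD-concern log OR 1.5 (0.27) | 19.7% | 10.2% | 70.5% | 84.9% |
| SD-concern log OR 3 (0.10) | 31.2% | 12.5% | 72.1% | 94.3% |
| Rarer covariates, unequal sites (0.09) | 48.1% | 10.2% | 75.5% | 89.6% |

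A further run at realised R-squared of about 0.19 gave Wald power of 71%.

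Under no effect, the likelihood-ratio test rejected in about 6-9% of trials at a common rate of 17.5% and in 13-16% at 5%. Firth's penalised-likelihood test had power of about 78-87% and type I error of about 2-7%, depending on the assumed covariates.

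**6. Interactions.** With four clinics and three or fewer pre-phase events, at least one clinic has none, whatever the clinic sizes. P(at most 3) = 0.110 + 0.249 + 0.276 + 0.198 = 83% (binomial, n = 43, p = 0.05). For therapy status, section 5.4 requires at least 40% in each group. An 18/25 split with 5% in both groups gives 1 - (1 - 0.95^18)(1 - 0.95^25) = 56% that one group has no pre-phase event.

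**7. Larger enrolment.** At 60+60 (an assumed equal split of 120), P(no pre-phase event) = 0.95^60 = 4.6%. Simulated Wald power with no population correlation between covariates and period is about 90%. The closed form at R-squared 0.20 gives SE = sqrt((1/(60 x 0.05 x 0.95) + 1/(60 x 0.30 x 0.70))/0.8) = 0.733 and power of 82%.

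**The case against.** **The Wald test is not in the protocol.** This stands. A reader might infer that the trial simply lacks its stated 80% power. The document does not support that, because a likelihood-ratio test in the same model exceeds 80%. The choice of test may also sit in a statistical analysis plan that is not at hand. What remains is that the stated model, rates and N do not fit together: one common test falls short on power, the other on type I error, and under either the period estimate is infinite in about one trial in nine.

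**The sample size might look miscalculated.** It is not. It agrees with a logistic or two-proportion formula inflated by 1/(1 - R-squared). The weakness is how poorly that approximation describes a Wald test of beta1 at a 5% rate.

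**Nine slopes is not fixed.** Correct. The covariates are examples, so nine is the count if all are used. A shorter list would reduce the any-coefficient figure but not the 11%.

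**The any-coefficient figures rest on assumed covariates.** Correct, hence the range. An infinite nuisance coefficient, such as one for site, need not make the period effect infinite.

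**Enrolment may reach 120,** and section 9.2 projects 57 per period over three months. This would largely remove the problem. But section 5.4 still plans 43 per period, and 86 is the figure powered on.

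**The sentence on other model forms might be read as licence for a rescue chosen after seeing the data.** It is general diagnostic wording and does not say that the primary model may be replaced.

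**This is a pilot of preliminary effectiveness.** That lowers the severity. It does not remove the point, since section 9.3 says the study is powered on Aim 2.

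**Conclusion.** The concern holds in limited form and should be fixed before analysis. On the protocol's own rates at 43+43, the period coefficient has no finite maximum-likelihood estimate in about 11% of trials, and this needs no assumption about covariates. Some coefficient is infinite in roughly 20% under moderate assumed covariate distributions, and in 30-50% under less favourable ones.

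Wald power is about 68-71% near R-squared 0.20 in most settings, 74.5% in one where SD concerns strongly predict the outcome, and 77% with no covariate correlation. The likelihood-ratio test reaches the stated power but rejects too often under the null, most of all if the event rate stays near 5%.

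The period-by-site and period-by-therapy interactions will often meet strata with no pre-phase event. The 83% for sites needs only the 5% rate and four clinics; any sharper figure would need clinic sizes, which the documents do not give.

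**What to change.** In section 9.2:

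- State that beta1 is estimated and tested by Firth penalised-likelihood logistic regression, with a profile penalised-likelihood confidence interval.
- Restate the power at 43+43 for that test, showing the assumed covariates, prevalences and R-squared.
- Label the period-by-site and period-by-therapy analyses as descriptive.
- Optionally, report a marginal risk difference as well, since the trial is sized on a difference in proportions.

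The cost is a few lines of text and a short simulation. No extra patients are needed, and the method is available in both R and SAS, the software the protocol names. The downsides are slight shrinkage of the odds ratio and no confirmatory interaction p-values. Firth is not the only defensible choice, but it keeps the covariate adjustment and gives a usable estimate and interval when the pre-phase has no events. Its type I error, about 2-7% in these simulations, should be reported with the restated power.

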## **9.3 aim 3 Statistical plan**

**Aim 3. Assess preliminary implementation outcomes and contextual factors associated with implementation of the standardized screening approach for SD.**

Analytic Plan: Because this is a pilot type 1 hybrid trial, analyses of implementation outcomes and factors in Aim 3 are descriptive, aiming to inform a future multicenter randomized hybrid trial. Using an explanatory mixed method design, we will first use descriptive statistics to analyze **quantitative survey data**, which will inform qualitative data collection. All quantitative analyses will be performed by the study statistician, with data summarized for the entire cohort, as well as by site, on therapy or survivor, patient gender, patient age and provider type. **Qualitative data analysis** be performed by the qualitative/D&I research and reviewed by the entire research team. Qualitative analysis will follow rapid content analysis methods and will integrate the CFIR framework, as described in Aim 1. Codes and quantitative results will be summarized in a joint matrix to support development of implementation strategies to strengthen future testing and delivery of the screening approach.

Sample Size: As a type 1 hybrid trial, this study is powered on Aim 2, but will explore preliminary implementation outcomes. Aim 3 **patient stakeholder** surveys will be administered in conjunction with Aim 2 post-implementation surveys to patients who received screening (maximum n=43). As this aim measures preliminary/exploratory implementation and is limited to those who received screening, we will not have a minimum sample size. Reasons for missed screening will be collected separately from providers. Aim 3 **medical stakeholder** surveys will be administered to consenting providers (anticipating an 80% response rate, approx. n=16-24), and Aim 3 semi-structured interviews with be completed with 10-15 providers directly involved in the screening intervention. At sites where only certain medical stakeholders are responsible for SD screening/follow-up, additional brief interviews assessing acceptability will be completed (n=5-10). Because the qualitative interviews will be focused on experiences with the screening approach and barriers/facilitators, we anticipate reaching thematic saturation with these sample sizes.^50^ User-centered design and qualitative research findings demonstrate that on average, 5 users/interviews will identify around 73-85% of all problems, and that groups of 10 find 95% of all problems (reaching near-saturation) when evaluating a design.^50,55^

# 10 SUPPORTING DOCUMENTATION AND OPERATIONAL CONSIDERATIONS

## **10.1 regulatory, ethical, and study oversight considerations**

### **10.1.1 informed consent/Assent process**

### **10.1.1.1 Consent/assent and Other Informational Documents Provided to Participants**

Consent/assent forms describing in detail the screening intervention, study procedures, and risks are given to the participant and written documentation of informed consent/assent is required prior to starting intervention/ administering study product.

Seattle Children’s Hospital and Children’s Hospital Colorado have different consents. Seattle Children’s Hospital does not allow compensation for provider participation whereas CHCO does. The Seattle ICF clarifies that there will be no cost to neither the participant nor the participant’s insurance for the research procedures and added their own required HIPAA language. Seattle ICFs clarifies that information is kept confidential.

### **10.1.1.2 Consent/assent Procedures and Documentation**

Informed consent/assent process will be initiated prior to the individual’s agreeing to participate in the study and continues throughout the individual’s study participation. Extensive discussion of risks and possible benefits of participation will be provided to the participants and their families.

Consent and assent forms will be IRB-approved and the participant will be asked to read and review the document. The investigator will explain the research study to the participant and answer any questions that may arise. All participants will receive a verbal explanation in terms suited to their comprehension of the purposes, procedures, and potential risks of the study and of their rights as research participants. Participants will have the opportunity to carefully review the written consent/assent form and ask questions prior to signing. The participants will have the opportunity to discuss the study with their surrogates or think about it prior to agreeing to participate. The participant will sign the informed consent/assent document prior to any procedures being done specifically for the study.

The participants may withdraw consent/assent at any time throughout the course of the trial. A copy of the informed consent/assent document will be given to the participants for their records. The rights and welfare of the participants will be protected by emphasizing to them that the quality of their medical care will not be adversely affected if they decline to participate in this study.

All Aims:

Informed consent/assent process will be initiated prior to the individual's agreeing to participate in the study and continues throughout the individual's study participation. Discussion of risks and possible benefits of participation will be provided to the participants in a private setting. The strictly voluntary nature of the study will be clearly stated in recruitment materials or invitations and in the verbal consent for stakeholder interviews. All participants will be provided with information about the study and researcher's contact information.

Consent and assent forms will be IRB-approved and the participant will be asked to read and review the document. The investigator will explain the research study to the participant and answer any questions that may arise. All participants will receive a verbal explanation in terms suited to their comprehension of the purposes, procedures, and potential risks of the study and of their rights as research participants. Participants will have the opportunity to carefully review the written consent/assent form and ask questions prior to participating in study procedures. The participants will have the opportunity to discuss the study with whomever they wish, and to think about it prior to agreeing to participate.

The participants may withdraw consent/assent at any time throughout the course of the trial. The rights and welfare of the participants will be protected by emphasizing to them that the quality of their medical care will not be adversely affected if they decline to participate in this study.

Medical stakeholder surveys, focus groups, and interviews (Aims 1 and 3): Study presentation by the study personnel through existing professional relationships between potential participants and site PIs. Consent for study and HIPAA will be obtained via REDCap. Importantly, participation confers no greater than minimal risk to participants.

Clinical Trial (Aims 2-3): The screening approach will be implemented clinic-wide, across all eligible patients as a new clinical care practice. This will be done by the clinic staff after appropriate training on use the screening approach. This is acceptable because it is not outside of usual care, which includes discussions of sexual health between clinical providers and patients, and because risks are minimal.

Patient stakeholder surveys and EHR data collection (Aims 1 and 2): Because the study and site PIs have existing clinical relationships with all eligible patients, waiver of HIPAA authorization will not be necessary prior to eligibility screening. Eligible patients will be presented the study by the study team at the conclusion of existing clinic visits or via phone within 4 weeks of eligible visits. Study team members contacting patients for study presentation will be members of the Center for Cancer and Blood Disorder.

As has been done in our prior research, to maximize privacy/confidentiality given the sensitive topic, and to encourage honest participation, patient participation in surveys (Aims 1-3) and EHR data collection (Aim 2-3) will occur under a waiver of parental consent. *Justification for waiver of parental consent:* For both the protection of the participant and the quality of the study parental/guardian consent will not be required. Given the low risk associated with participation in a survey study, we request parental consent to be waived for minor participants. This study poses no more than minimal risk (no greater than that encountered within routine history and physical examination). Inability to administer this survey without parental consent will severely bias the findings: 1) The sample may be biased as only those patients most comfortable with sexual health discussions (as those they might have with their parents) would be willing to participate if parental consent were required, and 2) Data collection may be biased by requiring parental consent, as adolescents may be concerned about confidentiality/safety. Subjects must be reassured that information they share, both in completing the screening approach in clinic and in completing research surveys, will be kept confidential and that participation itself is confidential.

